## Discussion

According to the 2021 Essential Maternal and Newborn Clinical Care Guidelines for Uganda, for a woman with a normally progressing pregnancy the standard recommendation is a minimum of eight antenatal visits [26].Contact 1: Anytime ≤ 12 weeks.Contact 2: 13–20 weeks of gestation.Contact 3: 21–28 weeks of gestation.Contact 4: 30 weeks of gestation.Contact 5: 34 weeks of gestation.Contact 6: 36 weeks of gestation.Contact 7: 38 weeks of gestation.Contact 8: 40 weeks of gestation.

In addition, participants will be instructed to come to the clinic every time they are ill and will be evaluated at this point too. Outcomes will be assessed at the delivery or/and at the discharge if admitted to the hospital for any other causes related with the pregnancy or malaria (Table 1).

**Table 1 Tab1:** Study time points

Time point	Study procedures and data collection
Recruitment (ANC visit)	– *Full questionnaire* administered by a trained healthcare worker to collect information on demographic (eg. age, area of residence), socioeconomic factors (eg. education, occupation), number of previous pregnancies,, bed net ownership and use, adherence to malaria chemoprevention, barriers to administration of IPTp, use of ITNs, risk perception of COVID-19 and Malaria will be administered – *Clinical examination* assessing the general wellbeing and nutritional status of the woman, along with routine measurements (including weight, height, auscultation, blood pressure and temperature). Gestational age will be assessed, when available, by obstretic ultrasound and, if unavailable, by pelvis examination performed by experienced midwives – *Collection of blood sample* that will be analyzed as follows: oMalaria diagnostic test with microscopy and, when positive, parasite count. Positive samples will be sent to the ISS. Molecular diagnosis will be performed to confirm microscopy results and to discriminate between *Plasmodium* species. *Plasmodium falciparum* positive samples will be analyzed for detection of single nucleotide polymorphisms in *P. falciparum* genes associated with artemisinin and SP resistance. Women diagnosed with malaria will be treated and followed according to Uganda Clinical Guidelines o HIV diagnostic test o Hemoglobin levels o Blood glucose levels o Syphilis testing (RPR) All women found to be HIV + at study entry will be referred for further evaluation and treatment

Delivery	– *Delivery information*: study staff will document details of the delivery, including date and time, type of delivery, estimated blood loss and any maternal, obstetrical or neonatal complications – *Fetal outcomes:* stillbirths, low birth weight, preterm birth – *Infant information:* Apgar score and birth weight with calibrated scales. At the time of delivery, women will undergo repeat rapid HIV testing based on national guidelines. If women are found to have become HIV-infected during pregnancy, both the mother and their newborn will be referred for care following local prevention of mother-to-child transmission guidelines [26] – Analyses of the Placenta Blood by microscopy to detect placental parasitemia

Data will be collected using semi-structured questioners and managed using REDCap electronic data capture tools hosted at “Catholic University of the Sacred Heart”, Rome, Italy [28], and will be recorded on standard study data collection forms and will be reviewed for accuracy and completion. Upon resolution of data forms errors/missing values, the form will be ready for data entry. The obtained results will be entered into a database. A database will be developed to accommodate data entry and management of the study's data. The database will be created with a standard data management software package, such as Microsoft Office. A file for each study form will be created.

### Ethical considerations

Pregnant women will be asked for written informed consent to participation to the study. In line with the Ugandan National Guidelines for Research involving Humans as Research Participants [29], women below the age of 18 will be considered emancipated minors. Every clinical outcome will be managed as per National Clinical Guidelines for the care of pregnant mothers. Counselling and related clinical support will be offered to participants who get pregnancy losses. This study will not introduce any clinical management strategies outside the national clinical guidelines.

We shall administer consent at two levels; first we shall administer and obtain consent for participation in the study and publication of future results and thereafter consent for collection and transportation of blood samples to Italy. The blood samples collected will be used only for the purpose of this study and will not be stored beyond the current study project. All unprocessed blood samples will be destroyed from the department of infectious disease, Italian National Institute of Health as biological sanitary waste, at the end of the project. The same standard of care will be guaranteed to all individuals irrespectively of participation. The dignity of study participants will be guaranteed by the investigators, as well as data confidentiality and the right to withdraw data and/or biological samples at any time. Consent to pregnant women and to mature and emancipated minors will be obtained according to Uganda Human Subjects Protection Guidelines [29].

For all malaria positive samples processed for molecular analysis in the present study, identifying information will be removed to provide appropriate protection of medical confidentiality and privacy. In this way, sensitive data cannot be linked or re-linked with identifiable human subjects, making anonymous each sample processed.

The polymorphisms analysis of the propeller domain of the *Pfk13, Pfdhfr* and *Pfdhps* genes will be performed by advanced amplifications techniques and subsequent Sanger sequencing in a highly specialized scientific laboratory. The blood samples collected in this study will be sent to a laboratory in the Italian National Institute of Health, Italy, in order to have access to the latest gene amplification techniques. To enhance local capacity building, one laboratory staff from Aber Hospital will be supported to attend a two weeks exposure at the reference laboratory in Italy.

The present study has been approved by the Lacor Hospital Institutional Research and Ethics Committee (prot. no LACOR-2022-95).

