**Discussion:**

The present study will explore the impact of COVID-19 pandemic on incidence of malaria and malaria-related adverse outcomes, along with the prevalence of resistance to artemisinin derivatives and to sulfadoxine-pyrimethamine. To our knowledge, this is the first study aiming to explore the combined effect of these factors on a cohort of pregnant women.

*Trial registration*: This study has been registered on the ClinicalTrials.gov public website on 26th April, 2022. ClinicalTrials.gov Identifier: NCT05348746.

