#### Antimalarial resistance population

To estimate the epidemiological burden of resistance to first-line drugs for treatment and prevention of malaria in pregnant women, a separate sub-population of women diagnosed with positive malaria parasitaemia will be recruited. Prevalence of antimalaria resistance will be evaluated with a cross-sectional analysis of genetic polymorphisms in plasmodium parasites isolated from blood samples collected for the period July 2022 to June 2024. Individuals eligible for this subpopulation will be all pregnant women presenting with microscopically confirmed *P. falciparum* malaria in the study sites. For individuals included in this population, clinical data will be collected, and blood samples to be sent to Italian National Institute of Health, Rome, for detection of genetic markers of resistance to artemisinin derivatives and sulfadoxine-pyrimethamine.

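### The rule that processed samples can never be re-linked to a woman conflicts with her right to withdraw them and, read literally, cuts genotypes off from SP history and hides repeat isolates

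*Protocol article*

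**What the plan says.** All of the following is in the protocol article.

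- **Ethical considerations**, scope of the rule: "For all malaria positive samples processed for molecular analysis in the present study, identifying information will be removed".
- **Ethical considerations**, stated consequence: "In this way, sensitive data cannot be linked or re-linked with identifiable human subjects, making anonymous each sample processed". No code or key is mentioned.
- **Ethical considerations**, the paragraph before, guarantees participants "the right to withdraw data and/or biological samples at any time".
- **Study design, Antimalarial resistance population**, collects both kinds of data on the same people: "For individuals included in this population, clinical data will be collected, and blood samples to be sent to Italian National Institute of Health". The objective there is descriptive: "Prevalence of antimalaria resistance will be evaluated with a cross-sectional analysis of genetic polymorphisms in plasmodium parasites".
- **Table 1** (recruitment and ANC rows) sends positive samples to the reference laboratory, where "Molecular diagnosis will be performed to confirm microscopy results". The ANC row provides for up to eight malaria screens per woman and puts no limit on how many of her positives are shipped. The row for spontaneous visits sends only the first sample taken before treatment.
- **Sample size estimation** gives a minimum of 203 pregnant women diagnosed with malaria, raised to 224 cases.
- **Background, resistance section**, cites a 2015 study in which the sextuple haplotype rose from 3.9% at baseline to 16.7% after one dose of SP.

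**The concern.** A right to withdraw a sample at any time needs someone to be able to find that sample. If nothing connects a processed sample to the woman who gave it, the promise cannot be kept after processing. Consent for collecting and shipping blood is sought as a separate step, so women would be agreeing to a right that the next paragraph removes.

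Two statistical consequences follow from the literal wording. First, genotype could not be set against SP exposure, although the article's own background suggests that exposure strongly affects sextuple-haplotype prevalence. Second, several isolates from one woman would be counted as if they came from different women, and nobody could detect it.

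The wording also matters because anonymisation cannot be undone. It has to be settled before samples are processed.

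**Working it through.** **1. Possible readings of the sentence.** The text can be taken three ways.

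| Reading | Withdrawal after processing | Genotype joined to SP history | Repeat isolates recognised | Does the sentence stand? |
|---|---|---|---|---|
| A. Study code, key retained | Possible | Yes | Yes | No, re-linking is possible |
| B. Study code stays with coded clinical data, key destroyed | Not possible | Yes, for data already recorded under the code | Yes, if the code identifies the woman and not only the tube | Yes, but the withdrawal right fails |
| C. No code | Not possible | No | No | Yes, but all three fail |

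The wording rules out re-linking and calls the samples anonymous, so it fits B or C better than A. Under every reading at least one statement in the article is untrue.

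**2. The plan's own sample size.** Inputs from Sample size estimation: p = 0.16 (expected SP resistance), d = 0.05, N = 10,525. Two-sided 95% gives z = 1.96.

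- n0 = z² p(1−p)/d² = 3.8415 × 0.16 × 0.84 / 0.0025 = 206.5
- n = N·n0/(n0 + N − 1) = 10,525 × 206.5 / (206.5 + 10,524) = 202.6, so 203
- 203 × 1.10 = 223.3, so 224

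The stated figures reproduce. The formula treats each observation as a separate woman, so unrecognised repeats break its assumption.

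**3. Illustration of repeat isolates.** The documents give neither the number of samples per woman (m) nor the within-woman correlation (r). Both are assumed here. The design effect is DEFF = 1 + (m − 1)r, and the half-width grows by √DEFF.

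Two starting points are shown. One is the planned margin of 5.0 points, which applies if the 10% allowance is used up by other losses. The other is 224 usable samples: 1.96 × √(0.16 × 0.84/224) = 4.80 points, without the finite population correction.

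| m | r | DEFF | From 5.0 | From 4.80 |
|---|---|---|---|---|
| 1.2 | 0.3 | 1.06 | 5.1 | 4.9 |
| 1.2 | 0.5 | 1.10 | 5.2 | 5.0 |
| 1.5 | 0.5 | 1.25 | 5.6 | 5.4 |
| 2 | 1 | 2.00 | 7.1 | 6.8 |

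The moderate cases are small. Only the extreme row, where every woman gives two identical isolates, is large.

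**4. Illustration of SP history.** Suppose the cited 3.9% and 16.7% applied to women without and with prior SP, and let w be the share with prior SP. The pooled prevalence is then 3.9 + 12.8w. At w = 0.25 it is 7.1%; at w = 0.75 it is 13.5%. That difference of 6.4 points comes from case mix alone and exceeds the planned margin. The values of w are assumed, and the two percentages come from one cited study. The point is only that a pooled figure is hard to interpret without SP history.

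**The case against.** Several counter-arguments have force.

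- **The sentence concerns identifiable subjects, and an article may leave coding details to the full protocol.** It does not say that a study code is removed, so reading B is open and SP history could still travel with the sample. This stands: loss of that linkage follows from the literal wording but is not a declared intention. It does not rescue the withdrawal right, and the objection here is to a rule the article states.
- **Withdrawal is blocked only after processing.** True. The guarantee nevertheless has no time limit.
- **Repeat entry is partly controlled.** The resistance population excludes women who took any antimalarial before recruitment, and spontaneous visits contribute only the first pre-treatment sample. Both limit repeats. However, the spontaneous-visit wording may mean first per episode, and the ANC row carries no limit. If the exclusion covers SP given for prevention, it would also remove the SP contrast; the article does not say whether it does.
- **The precision loss is assumed and modest.** Accepted. It is an illustration only.

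A reader might also draw stronger conclusions that the article does not support:

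- **That the rule defeats the study's overall aim.** The claim that "this is the first study aiming to explore the combined effect of these factors on a cohort of pregnant women" is one general sentence in the abstract. The COVID-19 component uses aggregate facility data for 2018 to 2021, while samples are collected from July 2022 to June 2024. Woman-level linkage could not join the two in any case.
- **That a resistance-by-outcome analysis is lost.** Data analysis names behaviour, IPTp adherence and IPTp regimen as exposures. It does not name genotype.
- **That PCR confirmation becomes impossible.** Shipped samples are smear-positive by selection, so the overall confirmed share can be computed without knowing whose they are. Only matching to an individual record is lost.

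**Conclusion.** The concern holds as an internal contradiction that should be corrected. The conflict between permanent unlinkability and withdrawal at any time needs no assumption beyond the wording, and it applies from the moment a sample is processed. The loss of the link to clinical data, and the inability to recognise repeat isolates, hold if the sentence means what it literally says and no study code survives.

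The cross-sectional prevalence objective remains estimable. What suffers is whether it is a per-woman figure and whether it can be related to SP history. On precision, the planned 5.0 points would become about 5.2 to 5.6 under moderate assumed repeat sampling; the documents allow no firmer figure.

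**What to change.** Replace the anonymisation sentence with a statement of pseudonymisation:

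1. Each sample carries only a study code, constant for the woman, and a visit number.
2. The reference laboratory receives no identifiers.
3. The key is held at the study site until database lock and then destroyed. The consent text should say that samples and sample-derived data can be withdrawn until that date.
4. PCR and genotype results are joined to the clinical record by code.
5. The resistance prevalence estimates use the first pre-treatment isolate per woman.

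The cost is an amendment to the ethics and consent wording, with no added procedure or visit. The downside is that the key and the coded data must be protected until the key is destroyed. The withdrawal right also acquires an explicit end date, which participants must be told.

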### Dissemination of results

Results from this research will be disseminated at various fora, including local and international scientific conferences, the Ministry of Health, technical working groups and meetings at district offices in Lango region involving participation of local leaders (Cultural, technical, and Political leaders). To better reach enrolled communities, the findings of the study will also be disseminated in places of worship and community health service points using the community outreaches being organized by CUAMM and the district local governments in Oyam and Kole districts. Findings will also be published in a peer reviewed journal.

## Data Availability

All data that will be generated or analysed during this study will be either included in the published article (and its supplementary information files) or will be made freely available to scientists wishing to use them for non-commercial purposes, without breaching participant confidentiality.

## Abbreviations

ACT: Artemisinin combination therapy
ANC: Antenatal care
CI: Confidence interval
COVID-19: Corona Virus Disease 2019
HIV: Human Immunodeficiency Virus
IPTp: Intermittent preventive treatment in pregnancy
LMICs: Low- and middle-income countries
MOH: Ministry of Health
NGO: Non-Governmental Organization
PNFP: Private not for profit
Pfdhfr: P. falciparum dihydrofolate reductase
Pfdhps: P. falciparum dihydropteroate synthase
Pfk13: P. falciparum kelch 13
RDT: Rapid diagnostic test
SP: Sulfadoxine-pyrimetamine
UDHS: Uganda Demographic and Health Survey
UNCST: Uganda national council of science and technology
WHO: World Health Organization
